### Recruitment

The invitation to participate will be made in the context of consultation, and subjects who agree to participate in the study will be given the free and informed consent form previously approved by the University and Hospital Ethics Committee.

### Outcomes and variables

Immediately after recruitment, all enrolled patients who agree to participate will sign the informed consent.

The subjects then proceed to the baseline data collection, intervention protocol, and final assessments (Fig. 1).

**Fig. 1 fig0001:**
[figure not shown]
Intervention schedule.

In the first contact, we evaluated functionality, health-related quality of life, and Self-Care of Chronic Illness Inventory—Patient Version, with three linked sequential behaviors captured in the critical concepts of self-care maintenance, monitoring, and management. Self-care maintenance addresses behaviors patients with a chronic illness use to maintain physical and emotional stability (e.g., medication adherence). In contrast, self-care monitoring involves observing oneself for signs and symptoms (e.g., checking blood pressure): self-care monitoring links or bridges between self-care maintenance and self-care management.

We will conduct a mixed methods evaluation, including a quantitative outcome evaluation to assess the effectiveness of the intervention and a qualitative and quantitative process evaluation to derive indications for future implementation in different clinical settings (Table 1).-Anthropometry: Weight evaluation will be done using a scale and height of a stadiometer. The International Society for the Advancement of Kinanthropometry (ISAK) protocol assessed waist circumference.-Chronic diseases will be evaluated based on the number, medication and measure evaluation.-``Self-Care of Chronic Illness Inventory - Patient Version'' (version 4) instrument which includes 20 items across three scales: (i) Self-Care Maintenance (8 items); (ii) Self-Care Monitoring (6 items); and (ii) Self-Care Management (6 items). All the responses are based on a 5-point Likert scale, with one being ``Never'' or ``Not Likely'' and five being ``Always'' or ``Very Likely'' [2];-The ``WHOQOL-BREF(PT)'' instrument, which comprises 24 facets (one item per facet) clustered into four domains, allows for the measurement of the quality of life of people following the World Health Organization criteria [4].-The ``CORE SET'' (version 4) instrument, the Elderly Nursing Core Set'', aims to classify the degree of elderly functioning, which is also capable of even establishing elderly ``nursing care needs'' [5,6].

**Table 1 tbl0001:** Measures and outcomes.

Measures and outcomes	Tools of assessment	Data source
Sociodemographic data	• Sociodemographic profile	- Sex, age, educational level
Anthropometric	• Weight scale • Stadiometer • Abdominal measuring tape • Body mass index	- Weight - Height - Abdominal circumference
Chronic diseases	• Medication • Sphygmomanometer • Blood samples • Glycemia dispositive • Finger oxygen device	- Number of diseases - Chronic medication - Mean blood pressure - Glycemia variation - Blood oxygen level
Health-related quality of life	• IWQOL-BREF	- 24 facets (one item per facet) clustered into four domains, allows for the measurement of the quality of life of people following the World Health Organization criteria
Self-care	• Self-Care Inventory of Chronic Illness Inventory – Patient Version	- 20 items across three scales: (i) Self-Care Maintenance (8 items); (ii) Self-Care Monitoring (6 items); and (ii) Self-Care Management (6 items). All the responses are based on a 5-point Likert scale, with one being ``Never'' or ``Not Likely'' and five being ``Always'' or ``Very Likely''
Elderly nursing core set (ENCS)	• Elderly functioning	- 28-item, self-report questionnaire that aims to investigate attitudes, behaviors and cognitions related to eating disorder symptoms

### Intervention description

A disease management and patient empowerment program will be developed based on quality standards. This program will promote self-care by encouraging specialist nurses to adopt an anticipatory approach and follow professional responsibility and prudence principles. Monitoring and intervention will focus on recognizing and empowering others by building interpersonal relationships and helping them develop knowledge and self-confidence. A specialist nurse will provide patients in the intervention group with management and lifestyle information. The self-care intervention program will include a range of techniques for managing different chronic diseases based on reports from older individuals with chronic diseases. The program consists of two sessions daily, with at least one month between each (Table 2, Table 3).

**Table 2 tbl0002:** Intervention planning.

	Unit of competence	Concepts of self-care	Self-care behaviors
Session 1	• Empowers the person and family/significant other, for the management of treatment • Promotes care for the person with chronic disease	Self-care maintenance Self-care monitoring Self-care management	- Lifestyle improvement - Motivation - Treatment adherence - Medication management - Comorbidities management - Physical activity - Hydration - Weight control - Body composition management - Smoking cessation - Alcohol use - Sleep improvement - Dietary intake - Psychosocial consequences
Session 2	• Empowers the person and family/significant other, for the management of treatment • Promotes care for the person with chronic disease	Self-care monitoring Self-care management	- Activity changes - Weight control - Body composition management - Managing symptoms - Medication changes - Smoking cessation - Alcohol use - Psychosocial consequences - Pain management - Managing dietary changes - Consulting healthcare provider - Nausea and vomiting management

**Table 3 tbl0003:** Self-care protocol.

1st evaluation	Baseline

2nd Evaluation	One month (post-intervention)
3rd Evaluation	Four months (post-intervention)

## Evaluation

We have three evaluations: baseline (before intervention), one and four months after intervention.

## Discussion

This is an innovative work that will allow this Research Center to be at the forefront of a pioneering work that can significantly contribute to the promotion of scientific research in the field of active and healthy aging research, improving the survey of needs, the development, monitoring, and Evaluation of nursing interventions, and the dissemination of good practices and innovation in older people with chronic diseases (multimorbidity) [7].

This project meets a new paradigm that has been assuming more significant and critical relevance: the construction of a ``health value model'' that aims to obtain results that promote positive changes in people's health conditions [8,9]. The form of Evaluation of this model is based on the recording of data throughout the care cycle. It focuses primarily on people's expectations and how much care has contributed (or not) to improving their health status.

The concept of self-care underlies nursing interventions at different levels and allows for the organization of care according to the needs of people aged 65 and older presenting multimorbidity [10]. Older people need personalized and comprehensive care, given the specificity of the health condition of the older person and, indirectly, through education regarding self-care, i.e., the promotion of good practices. Its scope may focus on health promotion or disease prevention, together with the older person and family caregiver, in managing their health condition, preferably at home (home-based care).

## Statistical methods

Several statistical analysis techniques will be used: psychometric, descriptive, and inferential. Confirmatory Factor Analysis techniques (application of Structural Equation Models), Multiple Linear Regression Methods and Ordinal Regression Methods will also be used. A confidence level of 95 % and an error of 4.5 % will be considered.

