## Abstract

Most aging populations report chronic illnesses, which are usually permanent or recurrent, significantly affect well-being and quality of life, require daily and consistent healthcare management, and last more than three months. Improved health outcomes and reduced healthcare costs are associated with self-care in treating chronic illnesses. The aim is to describe a protocol using a self-care intervention in a person with a chronic disease. A longitudinal study will be conducted with 40 patients. This article describes a protocol for a self-care intervention in a person with a chronic disease. The outcome measures will be compared with measures after the intervention in three different chronologic times. Randomization will be used to assign participants to the intervention group. The present study is expected to generate significant information about the role of self-care intervention in persons with chronic disease.

Specifications table

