**Table utbl0001:** 

Subject area	Medicine and Dentistry
More specific subject area	Lifestyles and health care; Health policies and research in health services; Research in patient-centered care
Name of your protocol	SELF-CARE IN THE PERSON WITH CHRONIC DISEASE
Reagents/tools	SELF-CARE OF CHRONIC ILLNESS INVENTORY WHOQOL-BREF(PT) CORE SET
Experimental design	A quantitative longitudinal study with 400 patients randomly selected. A protocol using a self-care intervention with adults registered in consultations of diabetes, pulmonology, and cardiology who have more than one chronic disease in the Hospital. In two different chronologic times, baseline measures will be compared with measures after self-care intervention. Participants' randomization will be determined to assign them to the intervention group.
Trial registration	The study protocol was registered in the Clinicaltrials.gov NCT06235593
Ethics	The study protocol was submitted to the Research Ethics Committee of the University and Hospital and approved under No. 20/23
Value of the protocol	• This protocol is essential to determine the nursing care needs of the elderly population sample according to the self-care deficits identified in the elderly population living in their own homes or the homes of relatives or friends in the district of Évora. • There needs to be more knowledge about the effects of self-care interventions. • This article is essential to contribute to the recommendations for self-care for older adults.

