### Sample size calculation

Considering the explorative nature of the study, a formal sample size analysis is not possible. However, we expected to collect 40 patients, selected from the hospital database based on the G*Power software. The number of participants was calculated as 33 cases by using linear multiple regression with *α* = 0.05 and 1 − *β* = 0.80. Considering a dropout rate of 20 %, the minimum sample size was therefore derived as 40 patients.

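### Confirmatory factor analysis is planned, but the only derived sample size (40 patients, calculated for regression) is too small to test the structure of the full instruments

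*Protocol article*

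**What the plan says.** The Statistical methods section of the protocol article lists psychometric, descriptive and inferential techniques and adds "Confirmatory Factor Analysis techniques (application of Structural Equation Models), Multiple Linear Regression Methods", together with ordinal regression. It names no instrument, factor structure, estimator or time point for the CFA. Its last sentence sets a 95% confidence level and a 4.5% error.

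The article gives two sample sizes:

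- Abstract: "A longitudinal study will be conducted with 40 patients".
- Sample size calculation: the number was "calculated as 33 cases by using linear multiple regression with" α = 0.05 and power 0.80, and after a 20% dropout allowance "the minimum sample size was therefore derived as 40 patients". The effect size and the number of predictors are not given.
- Specifications table: "A quantitative longitudinal study with 400 patients randomly selected".

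The Outcomes and variables section describes the self-care inventory, "which includes 20 items across three scales" (8, 6 and 6 items, 5-point responses), and a quality-of-life instrument of 24 single-item facets in four domains. Table 1 gives 28 items for the functioning instrument.

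**The concern.** A sample size derived for a regression with few predictors does not carry over to a factor model of 20 or 24 items. Loadings, residual variances and factor correlations must all be estimated, and the usual fit test relies on a large-sample approximation.

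At 40 patients a sound instrument could appear to fit badly, and the estimates would be too imprecise to show otherwise. The self-care inventory measures what the primary objective addresses. A misleading structural result on that instrument would therefore touch the scale by which the intervention is judged.

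**Working it through.** **1. The plan's own figure.** Starting from 33 cases with 20% dropout, 33 × 1.20 = 39.6, which rounds up to 40 and matches the article. Dividing by the retained fraction gives 33 / 0.80 = 41.25, so 42; the difference of two patients does not matter here. With 20% loss, 40 × 0.80 = 32 remain. The base of 33 cannot be recomputed uniquely without the effect size and the number of predictors. As a guide, the noncentral F gives N = 31 for f² = 0.35 with two predictors, and N = 34 for f² = 0.25 when one coefficient is tested. Nothing in the derivation refers to a factor model.

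**2. Free parameters.** For a simple-structure model with correlated factors and factor variances fixed at 1, the count is loadings + residual variances + factor correlations = 2 × items + f(f − 1)/2.

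| Model | Calculation | Free parameters |
|---|---|---|
| Self-care inventory, 20 items, 3 factors | 20 + 20 + 3 | 43 |
| Quality of life, 24 facets, 4 factors | 24 + 24 + 6 | 54 |
| Functioning instrument, 28 items, 1 factor (assumed) | 28 + 28 | 56 |
| One self-care scale, 8 items, 1 factor | 8 + 8 | 16 |
| One self-care scale, 6 items, 1 factor | 6 + 6 | 12 |

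If the 5-point self-care items are treated as ordinal, the three-factor model has 20 loadings + 20 × 4 thresholds + 3 correlations = 103 parameters.

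The three-factor model of 20 items is identified: 20 × 21 / 2 = 210 moments, so 210 − 43 = 167 degrees of freedom.

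**3. Behaviour of a true model.** Data were simulated from a correctly specified three-factor, 20-item model and fitted by normal-theory maximum likelihood, with 300 replicates per sample size. The loadings of 0.6, factor correlations of 0.5 and normal data are assumptions; the article gives no such values.

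| | N = 33 | N = 40 | N = 400 |
|---|---|---|---|
| True model rejected by nominal 5% chi-square test | 94% | 81% | 6% |
| Mean RMSEA | 0.109 | 0.085 | 0.008 |
| RMSEA above 0.08 | 91% | 63% | 0% |
| SD of a loading (true 0.6) | 0.17 | 0.16 | 0.05 |
| Central 95% of a factor correlation (true 0.5) | 0.06 to 0.86 | 0.11 to 0.79 | 0.41 to 0.59 |
| Improper solutions | 2% | 2% | 0% |

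All fits converged.

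**4. Analytic cross-check.** A Bartlett-type multiplier is (N − 1) − (2p + 5)/6 − 2k/3. With N = 40, p = 20 and k = 3 it is 39 − 7.5 − 2 = 29.5. The uncorrected statistic then has a mean of about 167 × 39 / 29.5 = 221 instead of 167. The 5% critical value on 167 df is 198.2; rescaled, 198.2 × 29.5 / 39 = 149.9, and a chi-square on 167 df exceeds that with probability 0.82. This agrees with the simulated 81%.

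**5. A simpler gauge of precision.** The Fisher interval for an inter-item correlation of 0.5 at n = 40 is tanh(0.549 ± 1.96/√37) = 0.22 to 0.70.

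**6. Which sample size the 4.5% error fits.** Taking it as the margin for a proportion of 0.5 at 95% confidence (an assumption), n = 1.96² × 0.25 / 0.045² ≈ 474.3, so 475. It would be 400 when sampling from a finite population of about 2,550. The margin is 15.5% at n = 40 and 4.9% at n = 400.

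**The case against.** The strongest reply is that 40 may be the wrong number. The specifications table says 400, and the 4.5% error, stated directly after the sentence that plans the CFA, fits 400 to 475 people and not 40. At 400 the simulated test rejects a true model in 6% of samples and the objection largely disappears. This stands, and it makes the point conditional. It does not remove it, because 40 is in the abstract and is the only number with a derivation.

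The second reply is that no model is named. The 43 and 54 parameters belong to joint models of each whole instrument. One-factor models per self-care scale need only 12 to 16 parameters with continuous items, fewer than 40. This also stands: the parameter comparison applies to the full-instrument models only. Correlations remain imprecise at n = 40 either way.

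A reader might infer from parameters outnumbering patients that the results would be uninterpretable, or that the models would often fail to converge. The working does not support that. The three-factor model is identified, every simulated fit converged and about 2% of solutions at N = 40 were improper. Ordinal data could behave worse, but this was not simulated.

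A reader might also infer that poor fit will be used to drop items or redefine outcome scales. The article does not say so, describes the instruments with fixed items and scales, and does not tie the CFA to the primary objective. Model details and scoring rules may properly sit in a fuller document. Finally, a baseline CFA would use all 40 patients, so the smaller number after dropout matters only for later assessments.

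**Conclusion.** The point holds in conditional form. If the sample is 40, a CFA of the full self-care or quality-of-life instrument would give unreliable fit tests and estimates too imprecise to confirm or reject the structure. For the three-factor self-care model, about 80% of samples would wrongly reject a true model, and a factor correlation of 0.5 could be estimated anywhere from about 0.11 to 0.79. These figures rest on assumed loadings of 0.6, factor correlations of 0.5, normal data and an uncorrected chi-square test.

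The conclusion does not extend to N = 400, and the parameter count does not apply to separate one-factor models per scale. What is wrong as written is that the article commits to this method alongside a sample size derived for a different analysis, while giving two sample sizes that differ tenfold.

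**What to change.** First reconcile the sample size across the Abstract, the Specifications table, the Sample size calculation and the 4.5% error in Statistical methods.

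If the number is 40:

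- remove CFA and structural equation modelling from the planned analyses;
- score each instrument by its validated version, fixed in advance;
- limit psychometrics to baseline internal consistency (alpha or omega with 95% confidence intervals), labelled descriptive;
- state that psychometric results will not alter the outcome scores.

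If the number is 400, CFA can stay, and the sample size section should be corrected to match.

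At 40 the change means less analysis work. The downside is that no structural-validity claim can be made from this sample.

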## Ethics statements

The work described has been carried out by the Ethical Committee of the University and Ethical Professional of the Hospital, approved with ethics protocol number 20/23. Participation was voluntary, with written informed consent obtained from all participants.

## Data Availability

Data will be made available on request. Data will be made available on request.
